**Discussion:**

This method would allow clinicians to take a pro-active attitude by performing a rapid psychophysical test before starting milnacipran treatment and would avoid unnecessary prescription while preventing therapeutic failure in patients who often face this recurrent problem.

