## Background

Fibromyalgia has a prevalence estimated at 2 to 5% of the general population in Europe [1] and in the United States of America [2] and is approximately seven times more common in women than in men [3]. Diagnostic criteria have been validated since 1990 by the American College of Rheumatology and have been enlarged in the 2010 revision to consider not only tender points but also cognitive problems and the extent of somatic symptoms [4]. The pathophysiology of fibromyalgia is uncertain but a dysfunction of descending pain inhibitory pathways [5-7] has been described as a cause or a consequence of the pathology [8]. These pathways originate in the brainstem and are involved in diffuse noxious inhibitory controls (DNICs) that are part of a central pain modulatory system relying on spinal and supraspinal mechanisms [9]. This pain modulatory system can be easily triggered and studied in experimental settings [10,11] using the conditioned pain modulation test, where the administration of two simultaneous painful stimuli typically results in pain inhibition [12,13]. Stimulation of DNICs is commonly used to evaluate any impairment of descending pain modulation.

Antidepressants have a mechanism of action that involves a number of neuromediators (serotonin, noradrenaline) within the brain-brainstem-spinal-cord axis and affects pain descending pathways [14]. Duloxetine and milnacipran are serotonin and norepinephrine reuptake inhibitors and have been approved for treatment of fibromyalgia by the Food and Drug Administration [15-17] for their analgesic properties [14]. Experiments on the safety, tolerability, and clinical benefits of long-term milnacipran use in patients with fibromyalgia have shown good results [18]. A review of four double blind studies focused on the efficacy of milnacipran in fibromyalgia [18]: a substantial improvement on global status was observed and more than 30% pain relief was obtained but only in 40% patients.

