### Sample size calculation

According to our previous work and a study of the literature [13], we calculate that a sample size of *n* = 24 patients per randomized group would provide 90% statistical power of detecting an absolute difference of 15 points in the primary outcome, that is, the conditioned pain modulation difference between milnacipran and placebo (with a standard deviation of conditioned pain modulation variation equal to 16 points), at a two-sided alpha level of 0.05. A total of 48 patients will be included.

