### Statistical analysis

Statistical analysis will be conducted on an intention-to-treat principle using Stata software, version 13 (StataCorp, College Station, TX, USA). A two-sided *P* value of less than 0.05 will be considered to indicate statistical significance. Baseline characteristics will be presented for each randomized group as the mean ± standard deviation or the median (interquartile range) according to statistical distribution for continuous data, and as the number of patients and associated percentages for categorical parameters. Comparisons between independent groups will be analyzed using the Chi squared or Fisher’s exact test for categorical variables, and by Student’s *t*-test or the Mann–Whitney test for quantitative parameters (notably primary outcome, temporal summation, test-stimulus intensity ‘pain 60/stimulus’, pain rating on the numeric pain rating scale, cognitive parameters, with normality verified by the Shapiro-Wilk test and homoscedasticity by the Fisher-Snedecor test. As suggested by Vickers and Altman [23], the primary analysis will be completed by an analysis of covariance considering conditioned pain modulation at 1 month as a dependent variable, and group and baseline value of conditioned pain modulation as independent parameters. Finally, to study whether the DNICs (assessed using the conditioned pain modulation test) in patients with fibromyalgia would be predictive of milnacipran efficacy, multivariate models such as regression analysis (milnacipran efficacy evaluated by conditioned pain modulation difference taken as a dependant variable [13]) will be performed considering the randomization group and the baseline values of conditioned pain modulation and pain as covariables. Secondarily, a sensitivity analysis concerning missing data will be considered to study their nature (not missing at randomization, missing at randomization and so on) and to propose the most appropriate imputation approach.

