## Discussion

Evaluation of predictive factors of pain development and pain alleviation is very important for treatment optimization [24]. Pain alleviation in fibromyalgia is very difficult, as the response to analgesics is very variable. Milnacipran is particularly recommended for the management of fibromyalgia [16] but only 40% of patients are relieved (30% less pain) [18]. Adding to this high variability in the response to milnacipran, discontinuation of treatment is also due to adverse events in 25% of patients compared with 12% in those receiving placebo [25]. Considering that many patients have no improvement of pain symptoms, it is therefore important to explore the status of the pain modulatory system and evaluate whether DNICs could be a predictive factor of the efficacy of milnacipran in patients with fibromyalgia. The comparison of the performance of descending inhibitory pathways when triggered by a painful stimulus before and after treatment gives information on the amplitude of pain modulation and control. It may help to predict non-responders, as shown for duloxetine [13], and identify the risk of developing chronic post-operative pain [26]. This study aims first to evaluate the state of functioning of the DNICs in patients with fibromyalgia and then to estimate if it might be a predictive factor of pain alleviation. If such an impact is demonstrated, clinicians could perform a simple psychophysical test to test the DNIC performance before prescribing milnacipran. Considering the tight links between chronic pain and cognitive impairment [19], the study will also assess the impact of milnacipran on several cognition domains. This approach could help to optimize treatment, would avoid useless prescription, prevent unnecessary adverse events, and, more generally, would prevent recurrent therapeutic failure in non-responder patients.

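### The analysis of whether baseline conditioned pain modulation (CPM) predicts milnacipran efficacy tests a regression coefficient for CPM change, which cannot support the per-patient prescribing use drawn from it

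*Protocol article*

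**What the plan says.** Prediction of milnacipran efficacy from baseline CPM is a secondary objective (Protocol article, Objectives). For it, the Statistical analysis section states that, to study whether descending inhibition "would be predictive of milnacipran efficacy, multivariate models such as regression analysis" will be performed. Efficacy is represented by the CPM difference as dependent variable, and the covariates are randomization group, baseline CPM and baseline pain. The only criterion of evidence in that section is general: a two-sided P "value of less than 0.05 will be considered to indicate statistical significance".

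The use foreseen for the result concerns individual patients. The Background says the information would allow the drug not to be prescribed where it is not expected to work. The Abstract's Discussion says that testing before treatment "would avoid unnecessary prescription while preventing therapeutic failure in patients who often face this recurrent problem". The main Discussion says: "If such an impact is demonstrated, clinicians could perform a simple psychophysical test to test the DNIC performance before prescribing milnacipran". The response level the article itself uses is pain relief: in the reviewed trials "more than 30% pain relief was obtained but only in 40% patients".

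**The concern.** The analysis and the conclusion answer different questions. A regression coefficient says that the mean outcome shifts with baseline CPM. A test used before prescribing has to separate patients who will get pain relief from those who will not.

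The stated model is two steps away from that. Its outcome is CPM change, not pain. And its outcome is computed from the predictor, since the change is the one-month CPM minus the baseline CPM. A significant coefficient for baseline CPM could therefore appear when baseline CPM says nothing about who benefits from the drug, and the article gives no other criterion by which the result would be judged. At stake is the clinical message of the trial, not its primary between-group comparison.

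**Working it through.** **Inputs from the article.** 24 patients per arm, 48 in total; SD of CPM change 16 points; difference 15 points; two-sided alpha 0.05 (Sample size calculation, Statistical analysis). 40% responders at 30% pain relief (Background, Discussion). Three covariates in the prediction model (Statistical analysis).

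**Assumptions of mine.** Bivariate normality of baseline CPM and the underlying response; visit-to-visit correlation of CPM between 0.5 and 0.9; equal SD at both visits.

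**1. The stated sample size.** n per arm = 2 × (1.960 + 1.282)² × 16² / 15² = 23.9, so 24, with 90.1% power (88.9% by the noncentral t). It reproduces, and it concerns the primary comparison: "24 patients per randomized group would provide 90% statistical power of detecting an absolute difference of 15 points in the primary outcome". No figure is given for the prediction objective.

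**2. Smallest association reaching P < 0.05.** r = t / √(t² + df).
- Planned model, 48 patients and three covariates, df = 44, t = 2.015: r = 2.015 / √(4.06 + 44) = 0.29, so r² = 8.5%. The residual SD falls only from 16 to 16 × √(1 − 0.085) = 15.3 points.
- Milnacipran arm alone, one predictor, df = 22, t = 2.074: r = 2.074 / √(4.30 + 22) = 0.40, so r² = 16%.

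**3. What such a correlation would mean for sorting patients, if it applied to pain response.** With responders defined as the top 40% of the underlying response, simulation under bivariate normality gives:

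| r | AUC | Sensitivity, 40% called positive | Sensitivity, 70% called positive |
|---|---|---|---|
| 0.29 | 0.63 | 51% | 80% |
| 0.40 | 0.68 | 56% | 83% |

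The AUC needs no cut-off. The sensitivities depend on one, and the article sets none; specificity falls as more patients are called positive.

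**4. Coupling of predictor and outcome.** With equal SDs and visit-to-visit correlation ρ, the correlation of change with baseline is −√((1 − ρ)/2): −0.50 at ρ = 0.5, −0.39 at 0.7 and −0.22 at 0.9. I simulated the stated model with 24 per arm, a uniform 15-point treatment effect and no treatment-effect modification:

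| ρ (assumed) | Baseline CPM coefficient significant | Group-by-baseline term significant, if added |
|---|---|---|
| 0.5 | 95% | about 5% |
| 0.7 | 78% | about 5% |
| 0.9 | about a third (31% to 34% across runs) | about 5% |

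So the baseline coefficient is often significant although every patient has the same expected benefit from the drug.

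**5. What accuracy estimates could show here.** 40% of 24 is about 10 responders and 14 non-responders on milnacipran. For an observed AUC A = 0.70, the Hanley-McNeil terms are A/(2 − A) = 0.538 and 2A²/(1 + A) = 0.576. Then SE² = [0.70 × 0.30 + 9 × (0.538 − 0.49) + 13 × (0.576 − 0.49)] / (10 × 14) = 0.0126 (unrounded terms), so SE = 0.112 and the 95% CI is 0.70 ± 1.96 × 0.112, or 0.48 to 0.92.

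**The case against.** The strongest reply is that the article never says a P value below 0.05 will make baseline CPM predictive. The significance sentence is generic, and the prediction sentence says only that models of a certain kind will be used to study the question. That is correct. A reader might infer a rule that a significant coefficient will be reported as a usable test, but no such rule is written. What stands is that no other criterion is given.

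Second, performance measures are commonly left to an analysis plan, which is not shown, and the wording leaves the choice of model open. This also stands: the absence of an AUC is not in itself the point. The point is that the outcome, the covariates and the clinical use are all stated in this document, and the use does not follow from the analysis.

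Third, the prescribing language is motivation rather than a decision rule. The main Discussion is conditional, and the objective is secondary. The Abstract, however, states the benefit without that condition.

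Fourth, the classification figures apply a correlation to pain response, which the planned model does not analyse. They are an illustration of what bare significance can mean. In particular, a reader might conclude that 44% to 49% of responders would be denied the drug. That follows only if the top 40% are called positive. Calling 70% positive gives a sensitivity of 80% to 83%, at the price of specificity, so the article does not support the larger claim.

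**Conclusion.** The concern holds as a mismatch between the stated analysis and the stated use. The planned model can give a significant baseline CPM coefficient that carries little or no information on who obtains pain relief.

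Two results give its size. The significance threshold of 0.29 would correspond to an AUC of about 0.63 if it applied to pain response, given bivariate normality and the article's 40% responders. And with no treatment-effect modification, coupling alone makes the coefficient significant in about a third to 95% of simulated trials, given equal SDs and visit-to-visit correlations of 0.9 to 0.5. The article states no such correlation, so the range is an assumption.

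A stronger true association would sort patients better than these figures suggest. The primary comparison and its sample size are unaffected. The change should be made, but the trial's main result does not depend on it.

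**What to change.** In Statistical analysis, relate baseline CPM to change in the numeric pain rating, which Table 1 schedules at both visits. In the milnacipran arm, report the ordinary AUC of baseline CPM for at least 30% pain reduction, the response level the article uses, with a 95% CI. Give the same figure in the placebo arm for contrast.

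Do not use a leave-one-out AUC for this single predictor. Simulated with 24 patients and 10 responders, it averaged 0.29 with no association, where 0.50 is right, and about 0.52 to 0.53 at r = 0.40, against an ordinary AUC of 0.68. Give sensitivity, specificity and negative predictive value only at a cut-off fixed in advance. A pass mark on negative predictive value is not advisable at this size: with 14 test-negative patients, about 13 would have to be non-responders for the exact lower limit to exceed the 60% non-response rate in unselected patients.

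In the Abstract's Discussion and the main Discussion, describe a positive result as identifying a candidate predictor that needs validation, not as a usable test before prescribing.

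The cost is a change of wording and a few lines of analysis, with no new data, visits or patients. The downside is wide intervals, roughly 0.48 to 0.92 for an AUC of 0.70, and a more modest clinical claim.

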**Methods/design:**

A randomized, double blind, clinical trial (NCT01747044) with two parallel groups, in 48 women with fibromyalgia, is planned in the Clinical Pharmacology Center, University Hospital, Clermont-Ferrand, France. Conditioned pain modulation (estimated with thermal stimuli using a numeric pain rating scale), the primary endpoint measure, is evaluated before and one month after treatment with milnacipran or placebo. Secondary outcome measures include the predictability of pain descending pathways performance for milnacipran efficacy, tolerance and cognitive function. Data analysis is performed using mixed models; the tests are two-sided, with a type I error set at alpha = 0.05. Not only will this trial allow estimation of the beneficial effect of milnacipran on pain and on descending pain pathways but it will also evaluate whether the performance of this modulatory system could be predictive of its efficacy in alleviating pain.

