Considering this large variability in response to milnacipran, it is expected that a number of patients will have no alleviation of pain: it would be beneficial for the patient to be able to predict the efficacy of milnacipran in pain associated with fibromyalgia before the prescription of the drug. It would also be important to evaluate cognitive function, which is frequently impaired in chronic pain [19]. This information would enable prescription of the drug to be avoided if no efficacy is expected, and would avoid therapeutic failure in patients who often stop their treatment because of lack of efficacy. Such a predictive approach has been performed with duloxetine in another pathology, painful diabetic neuropathy [13], where the authors have shown that pain alleviation may be predicted from pre-treatment conditioned pain modulation. Such an approach is quite interesting in the context of milnacipran as DNICs are involved in the mechanism of action of both drugs [12,17]. In this trial, we set the mechanistic hypothesis that (1) milnacipran restores the function of descending inhibitory pathways and concomitantly decreases the pain experience in fibromyalgia patients, and (2) this efficacy could be predicted from the performance, before treatment, of pain descending pathways when activated by conditioned pain modulation.

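### The prediction model takes change in conditioned pain modulation (CPM) as efficacy and regresses it on baseline CPM, so it does not address pain relief and its baseline coefficient is not evidence of prediction

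*Protocol article*

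**What the plan says.** The aim is stated in terms of pain. The abstract (Methods/design) says the trial will "evaluate whether the performance of this modulatory system could be predictive of its efficacy in alleviating pain", and the Discussion says it will "estimate if it might be a predictive factor of pain alleviation". The Background describes reference [13], a duloxetine study, as showing that "pain alleviation may be predicted from pre-treatment conditioned pain modulation".

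The Statistical analysis section specifies something else. It has "milnacipran efficacy evaluated by conditioned pain modulation difference taken as a dependant variable [13", and the covariates are randomised group, baseline CPM and baseline pain. The Conditioned pain modulation section defines the difference as CPMv3 − CPMv1, the one-month value minus the baseline value. (That section calls the one-month assessment visit 3 and Table 1 calls it visit 2; it is called the one-month visit below.)

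The numeric pain rating scale is recorded at both visits (Table 1). In the analysis it appears in a between-group comparison and, at baseline, as a covariate. No group × baseline CPM term is named.

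**The concern.** There are two separate faults.

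- **Outcome.** The question is about pain relief and the dependent variable is change in CPM. Even a perfectly estimated model would not show who gets less pain. The section cites [13] for this choice, yet on the protocol's own description that study predicted pain alleviation.
- **Baseline on both sides.** CPMv1 is a covariate and is also subtracted in the outcome. A non-zero coefficient is then expected from imperfect repeatability alone, in the placebo arm as much as in the milnacipran arm.

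Prediction is the first secondary objective and the second half of the stated hypothesis. The Discussion would use a positive answer to support testing patients before milnacipran is prescribed. A coefficient produced by regression to the mean could be read as that positive answer.

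**Working it through.** **The plan's own figure.** The inputs, all from Sample size calculation, are a difference of 15, SD 16 ("with a standard deviation of conditioned pain modulation variation equal to 16 points", read as the SD of the change), two-sided alpha 0.05 and power 90%.

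n per group = 2 × (1.960 + 1.282)² × 16² / 15² = 2 × 10.51 × 256 / 225 = 23.9, so 24. Normal-approximation power at 24 is 90.1%; the noncentral t gives 88.9%. The stated 24 per group reproduces.

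**Algebra of the prediction model.** Let X be baseline CPM, Y one-month CPM, r their within-arm correlation, and k = SD(Y)/SD(X).

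1. Regressing Y on group, X and baseline pain gives a coefficient b for X. Regressing Y − X on the same terms leaves the residuals and the group coefficient unchanged and gives b − 1 for X. The stated model is therefore the protocol's own analysis of covariance with baseline pain added. Testing its baseline coefficient against 0 tests whether b = 1.
2. With baseline pain unrelated to CPM, b has expectation r·k, so the coefficient in the stated model has expectation **r·k − 1** in each arm. With k = 1 this is −(1 − r): −0.5 at r = 0.5 and −0.3 at r = 0.7. It is zero only if r·k = 1.
3. The residual SD is SD(Y)·√(1 − r²). The expected size of the t statistic is therefore roughly |r·k − 1| / (k·√(1 − r²)) × √48. The SD of 16 cancels, so the rate depends on r, k and the sample size.
   - k = 1, r = 0.5: 0.5 / 0.866 × 6.93 = 4.0, against a critical value near 2.0.
   - k = 1.25, r = 0.7: 0.125 / (1.25 × 0.714) × 6.93 = 0.97.

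**Simulation.** The stated model was fitted by ordinary least squares with 24 per arm, SD of change 16, and the same drug effect (zero or 15 points) for every patient, so that baseline CPM does not modify the effect. There were 3000 or 4000 replicates per setting; runs differ by two to three percentage points. The share of trials with baseline CPM significant at two-sided 0.05 was:

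| r (assumed) | k = 1 | k = 1.25 |
|---|---|---|
| 0.3 | about 99% | – |
| 0.5 | about 95% | 62% |
| 0.7 | about 77% | 15% |
| 0.8 | about 57% | 5% |
| 0.9 | about 31% | – |

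At k = 1.25 and r = 0.8, r·k = 1 and the artefact vanishes, as step 2 predicts. If k is below 1, the expected coefficient is further from zero and the rates are higher.

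**Tests that keep their level.** These used k = 1, r from 0 to 0.9, and no true prediction.

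- Group × baseline CPM with CPM change as outcome: 4.3–5.4%. Subtracting X does not alter an interaction coefficient.
- Change in pain as outcome: 4.5–5.8% for baseline CPM and 4.0–5.5% for group × baseline CPM. This assumed a pain SD of 20 and a pre/post correlation of 0.5, neither of which is in the protocol.

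**The case against.** - **CPM change is part of the hypothesis.** Hypothesis (2) in the Background speaks of predicting the efficacy described in (1), which joins restored descending inhibition with reduced pain. This stands in part: CPM change is not foreign to the hypothesis, but it is only half of it. The abstract and the Discussion name the other half, pain alleviation, as what is to be predicted.
- **The wording leaves other models open.** The section offers regression as an example. That frees the type of model, but the dependent variable is named outright.
- **A reader might infer that the analysis is bound to yield a spurious predictor.** The protocol does not support that. It gives neither r nor the SD ratio, and the rate runs from about 99% down to the nominal 5% over plausible-looking combinations. A near-certain result needs low r with equal or falling variance.
- **A reader might infer that pain is never analysed.** It is compared between groups. What is absent is any stated model linking change in pain to baseline CPM.
- **A reader might say baseline CPM predicts nothing in these simulations.** For r > 0 it does predict one-month CPM. The null is narrower: it does not modify the drug effect.
- **This is a secondary objective.** True. The primary comparison, its analysis of covariance and the sample size are untouched, and so is the group coefficient in this model.

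**Conclusion.** The concern holds. The named dependent variable does not match the stated aim, and this follows from the text alone with no assumption. The baseline CPM coefficient in the stated model cannot be read as prediction of milnacipran efficacy, because its expected value is r·k − 1 in both arms when baseline CPM does not modify the drug effect.

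How often it would be significant is conditional. At 24 per group with equal SDs, it is about 99% at r = 0.3, falling to 31% at r = 0.9. It is lower if CPM variance rises by one month and higher if it falls. These rates rest on assumed r and k, and on the 16 points being the SD of change (though the 16 itself does not drive them).

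Replacing the outcome alone would not be enough. A baseline CPM slope pooled over milnacipran and placebo patients is prognostic; a claim about the drug needs the interaction with group. The defect is confined to the prediction analysis.

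**What to change.** In Statistical analysis, replace the definition of efficacy used for the prediction question:

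- **Dependent variable:** numeric rating scale pain at one month, adjusted for baseline pain (or its change from baseline).
- **Terms:** group, baseline CPM, baseline pain, and group × baseline CPM.
- **Inference:** rest any statement that baseline CPM predicts milnacipran efficacy on the interaction. Report it as exploratory with its confidence interval, since an interaction has limited power with 48 patients.
- **Restriction:** state that the baseline CPM main effect in a model of CPM change will not be interpreted as prediction. If CPM change is kept as a supporting outcome, the interaction is again the term to read.

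The cost is analysis wording only. Table 1 already schedules the pain scale and the CPM test at both visits, so no new measurement, visit or patient is needed, and the primary analysis and sample size stay as they are.

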### Objectives

The primary objective of this trial is to assess whether milnacipran has an influence on DNIC status, by measuring if there is a difference between the results of the conditioned pain modulation test in milnacipran and placebo groups.

The secondary objectives are to assess:Whether the DNIC status could be predictive of milnacipran efficacy in fibromyalgia,The evolution of pain threshold with milnacipran,The impact of milnacipran on cognitive parameters; comprehension tests, executive function, memory, attention and decision making,Tolerance towards milnacipran.

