### Conditioned pain modulation

Conditioned pain modulation is evaluated before treatment randomization (visit 1, CPMv1) and after 1 month treatment (visit 3, CPMv3). The milnacipran and placebo differences (CPMv3 − CPMv1) are then compared. With pain intensity rated by the patient on a numeric scale from 0 (no pain) to 100 (worst pain possible), the conditioned pain modulation is obtained with the following experiment. An Advanced Thermal Stimulator thermode (Medoc Ltd, Ramat Yishai, Israel) is applied to the volar side of the patient’s dominant forearm. The Medoc PATHWAY system delivers stimulation at the predetermined pain threshold for 10 seconds and the patient rates her pain using the numeric scale. Then the Medoc PATHWAY system delivers a stimulus at the same temperature for 30 seconds and the patient rates her pain using the numerical scale. After the end of these two stimuli (15 minutes), the patient puts the non-dominant hand into a water bath at 46.5°C for 60 seconds. After having dried her hand, the patient has a similar sequence of stimuli for 10 and 30 seconds with pain evaluation using the numeric pain rating scale. The aim of this test is to trigger the stimulation of pain descending pathways. If these pathways are functional, the second series of stimuli will be less painful than the first one because of the inhibitory effect on pain stimuli. It is the reverse if these pathways are not functional, as described in a number of chronic pain situations including fibromyalgia [11,21]. The amplitude of the conditioned pain modulation is given by the difference between the pain scores on the numeric pain rating scale before and after the immersion of the non-dominant hand.

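### The model for predicting milnacipran efficacy names no group-by-baseline-CPM term, so as listed it cannot separate prediction of drug response from prognosis in both arms

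*Protocol article*

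**What the plan says.** All references are to the protocol article.

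- **Background** states the second hypothesis: "this efficacy could be predicted from the performance, before treatment, of pain descending pathways when activated by conditioned pain modulation".
- **Objectives** lists as the first secondary objective: "Whether the DNIC status could be predictive of milnacipran efficacy in fibromyalgia".
- **Statistical analysis** assigns the method: "multivariate models such as regression analysis", with "milnacipran efficacy evaluated by conditioned pain modulation difference taken as a dependant variable". These models "will be performed considering the randomization group and the baseline values of conditioned pain modulation and pain as covariables".
- **Conditioned pain modulation** defines that dependent variable: "The milnacipran and placebo differences (CPMv3 − CPMv1) are then compared". It is a change score, so it contains baseline CPM.
- **Intended use.** The Discussion part of the abstract speaks of "performing a rapid psychophysical test before starting milnacipran treatment and would avoid unnecessary prescription". The main Discussion says that, if such an impact is shown, "clinicians could perform a simple psychophysical test to test the DNIC performance before prescribing milnacipran".

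The article nowhere mentions an interaction, a test of effect modification or a comparison of slopes between arms. The analysis of covariance that supports the primary analysis also contains only group and baseline CPM.

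**The concern.** Whether baseline CPM predicts the efficacy of milnacipran is a question about how the milnacipran–placebo difference varies with baseline CPM. A model with group, baseline CPM and baseline pain as separate terms holds that difference constant, so it assumes away what the objective asks. Its baseline-CPM coefficient shows which patients change, whichever capsule they took.

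The stake is the use that the article proposes. If CPM relates to outcome equally on drug and placebo, a significant coefficient could be taken as grounds for a test before prescribing, although the drug effect is the same at every CPM value. In the opposite case, where CPM matters only under milnacipran, the common slope averages the two arms and shows about half of the true relation. The trial has a randomized placebo arm, which is what allows the two cases to be told apart, but the listed model does not use it for that.

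**Working it through.** **1. The article's own figure.** Inputs from Sample size calculation: difference 15, SD 16, two-sided alpha 0.05, power 90%.

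n per group = 2 × (1.960 + 1.282)² × 16² / 15² ≈ 23.9, so 24. The normal approximation gives 90.1% power at 24. The t-test version gives 24.9 per group, and 88.9% power at 24. The stated size reproduces and does not depend on the point below.

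**2. What the listed model estimates.** Let D = CPMv3 − CPMv1, G = group (0 placebo, 1 milnacipran), C = baseline CPM, P = baseline pain.

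- As listed: D = b0 + b1·G + b2·C + b3·P + error. The drug effect is b1 at every C, and b2 is one slope for both arms.
- With the product: D = b0 + b1·G + b2·C + b3·P + b4·G·C + error. The drug effect is b1 + b4·C. The slope is b2 on placebo and b2 + b4 on milnacipran.

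Only b4 addresses the objective. With 1:1 allocation, b2 in the listed model is about the mean of the two arm slopes. A slope of 0 on placebo and 0.5 SD on milnacipran gives (0 + 0.5)/2 = 0.25 SD.

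**3. Effect of the stated dependent variable.** Assume equal CPM variance s² at both visits and visit-to-visit correlation r. The article gives no value for r.

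- The slope of D on C is r − 1, which is non-zero unless r = 1.
- The correlation of D with C is −√((1 − r)/2): −0.59, −0.50 and −0.39 for r = 0.3, 0.5 and 0.7.
- Replacing CPMv3 by D as outcome lowers b2 by exactly 1 and leaves b4 unchanged, because C is in the model. The built-in link therefore distorts b2 but not b4.

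**4. Simulated rejection rates.** 24 per arm, two-sided 5%, a group effect present, and no modification of the drug effect.

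| Assumption | Baseline-CPM coefficient, listed model | Added interaction |
|---|---|---|
| Outcome D, r = 0.3 | about 99% | about 5% |
| Outcome D, r = 0.5 | about 95% | about 5% |
| Outcome D, r = 0.7 | about 78% | about 5% |
| Generic outcome, same prognostic correlation in both arms: 0.3 / 0.4 / 0.5 | about 54% / 79% / 95% | about 5% |

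The first three rows use the outcome that the article states. The last row shows that the problem remains with an outcome that does not contain baseline CPM.

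**5. What the interaction can detect.** Assume a slope on milnacipran only, in outcome SD per SD of baseline CPM. The lower figure sets the residual SD to 1 in both arms; the upper sets the total SD to 1 in each arm.

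- Slope difference 0.5 SD: power about 36–41%.
- Slope difference 0.7 SD: power about 60–71%.

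In CPM points, with an assumed residual SD of 16, the standard error of b4 per SD of C is about 16 × √(2/24) = 4.62. On 43 degrees of freedom, 80% power then needs a slope difference of about 13.2 points per SD of baseline CPM, and 90% needs about 15.3. The primary analysis is sized for a whole treatment effect of 15 points.

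**The case against.** The strongest reply is that the article lists variables, not a full model. It writes of models in the plural and gives regression as an example. It does not say main effects only, and it does not name the coefficient that answers the objective. An unseen analysis plan could add the product, and the form of a secondary regression is often settled there.

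Part of this stands. A reader might infer that the authors ruled out an interaction or chose the common slope as their test. The text supports neither, and the rejection rates above apply only if the listed terms are fitted as they stand and the baseline-CPM coefficient is read as the answer. But the example wording loosens the type of model, not the list of terms. The article went as far as naming that list, and the one term that the objective needs is not on it.

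A second reply is that the interaction has low power. It does. That is a reason to report the slope difference with its interval as exploratory, not to test a different quantity.

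A third is that the clinical claim is hedged. The main Discussion is conditional and the objective says only that CPM could be predictive; the abstract is firmer. The hedging limits the harm but does not make the listed model informative about drug response.

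**Conclusion.** The point holds for the secondary predictive objective. As listed, the model yields one prognostic CPM slope. It cannot show that baseline CPM predicts the efficacy of milnacipran, and it cannot support the proposed test before prescribing. With the stated change score and no modification of the drug effect, the slope would be significant in roughly 78–99% of trials, against about 5% for the interaction. These rates rest on assumed correlations of 0.3 to 0.7, equal CPM variance at both visits and normal data; the article gives no values.

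Two stronger readings are not supported. A reader might infer that the trial's main result is compromised, but the primary comparison, its analysis of covariance and the sample size do not depend on this model. A reader might also treat this as an error in a model for pain relief, but the stated dependent variable is the change in CPM and the article describes no pain-change prediction model. The lack of an interaction matters with either outcome. The plan should be corrected here, but this is not a fault that puts the trial at risk.

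**What to change.** In the Statistical analysis section, add randomization group × baseline CPM, with CPM kept continuous, to the prediction model, whatever its dependent variable. State that the secondary objective is answered by that term. Report the CPM slope in each arm and their difference with a 95% CI. State that the common or baseline-CPM coefficient alone is not evidence of prediction of drug response. Label the analysis exploratory, give the power range above with its assumptions, and limit the pre-prescription claim in the abstract and the Discussion accordingly.

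The cost is one model term and a few sentences. It needs no new data, no extra patients and no change to the primary analysis. It can be fixed before unblinding; the article reports 26 of 48 patients recruited at the time of writing. The real cost is a weaker claim: with 24 per group, only a large difference in slopes is likely to be detected, and a non-significant interaction would not show that CPM is uninformative.
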